## Introduction

### Background and rationale {6a}

Oocyte aneuploidy is a major contributor to age-related fertility decline and a principal cause of pregnancy loss. Over the past decades, a global shift in reproductive behavior—most notably delayed childbearing—have increased the proportion of conceptions in older women and the incidence of age-associated fertility challenges [1]. Multiple factors contribute to these difficulties, among which declining oocyte quality—characterized by meiotic chromosome segregation errors—is a leading determinant and increases the risk of aneuploidy [2]. Epidemiological and clinical studies consistently show that the prevalence of aneuploid metaphase II oocytes rises sharply after the mid-30 s, with rates more than doubling in women beyond 34 years of age [3, 4]. Although postfertilization mitotic errors also contribute to chromosomal abnormalities, current evidence strongly supports that maternal age-related meiotic disturbances constitute the predominant origin of embryo aneuploidy [3, 5].

Proposed interventions to delay ovarian aging such as intraovarian stem-cell or platelet-rich plasma procedures remain investigational, and none has yet been proven in clinical trials to preserve oocyte genomic stability with advancing age [5, 6]. Assisted reproductive technologies (ART) including genetic testing for aneuploidy (PGT-A) permit selection of euploid embryos and inform transfer strategies but do not reduce the initial high frequency of aneuploid embryos seen in AMA. Current clinical guidelines advise PGT-A and frozen single embryo transfers for women with age-related fertility concerns [7]. However, embryo usability declines sharply after age 43 following PGT-A, underscoring the need for upstream biological interventions to improve oocyte quality at its source.

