#### Secondary outcome measures

Secondary outcome measures are the clinical pregnancy rate, miscarriage rate, and live birth rate.Clinical pregnancy rate: The ratio of the clinical pregnancy (intrauterine gestation sac with a fetal heart beat) number to the number of patients who received embryo transferMiscarriage rate: The ratio of the number of nonviable pregnancies before 28 weeks of gestation to the number of clinical pregnanciesLive birth rate: The ratio of the number of normal fetuses delivered after 28 weeks of gestation to the number of patients who received embryo transfer

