### Sample size {14}

Among women of AMA (38 ≤ age ≤ 42 years) undergoing treatment at this center, the current euploid blastocyst rate (defined as the number of euploid blastocysts per mature oocyte retrieved) is approximately 10%. This study is designed to increase this euploid rate to 17% with a significance level (α) of 0.05. To achieve this, each group is expected to include 371 mature oocytes, accounting for an estimated 10% dropout rate. This results in a final target of 408 mature oocytes per group. Given the average mature oocyte yield per cycle in women aged 38–42 years is approximately 5.45 oocytes, the study anticipates enrolling approximately 150 cycles in total.

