### Adverse event reporting and harms {22}

All AEs, whether solicited or spontaneously reported, will be monitored and recorded throughout the trial. Participants will be instructed to report any discomfort, unexpected symptoms, or complications during and after the intervention period. AEs will be assessed by the clinical research team for severity and potential association with the study intervention. Serious adverse events (SAEs) will be reported to the institutional ethics committee within 24 h of identification. All AEs and SAEs will be documented in the case report forms and the study database. If necessary, the principal investigator may suspend or discontinue the intervention for the affected participant.

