## Discussion

AMA is strongly associated with oocyte aneuploidy, which remains a major cause of implantation failure, miscarriage, and reduced live birth rates. Emerging evidence has highlighted the MVA pathway as a key regulator of oocyte meiotic maturation and genomic stability. Previous studies demonstrated that disruption of this pathway in granulosa cells is associated with impaired LHR and EGF signaling, leading to defective meiosis and increased aneuploidy [8]. In animal models, supplementation with MVA metabolites has been shown to mitigate meiotic errors, restore proper chromosome segregation, and reduce aneuploidy rates in aging oocytes [8]. These preclinical findings suggest that maintenance of MVA pathway integrity is critical for safeguarding oocyte quality during reproductive aging. Building on this evidence, the present study represents the first randomized controlled trial (RCT) to evaluate MVA supplementation in human-assisted reproduction. By directly translating preclinical discoveries into a clinical setting, this trial seeks to test whether short-term MVA supplementation during the pre-fertilization stage can enhance oocyte competence and increase the yield of euploid embryos in women of AMA.

A RCT was selected as the study design as it represents the gold standard for clinical research, effectively minimizing bias and providing the highest level of evidence for causal inference. A within-subject controlled approach was further adopted, whereby COCs from the same stimulation cycle are randomly allocated to MVA-supplemented or standard fertilization medium. This strategy maximizes statistical efficiency by controlling for inter-individual variability and thereby enhances the ability to detect the true effect of MVA supplementation. Women aged 38–42 years were specifically targeted as younger patients show low baseline aneuploidy, while women above 42 typically yield insufficient oocytes for analysis. This choice is also consistent with clinical practice guidelines, which recommend considering preimplantation genetic screening in women over 38 years [9]. The intervention parameters (50 µM for 4 h before insemination) were chosen based on effective conditions in animal studies and are readily integrated into routine IVF/ICSI practice.

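### The live birth rate counts normal fetuses over women, so as written it is neither a per-woman proportion nor a count of live births

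*Protocol article*

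**What the plan says.** Under Outcomes {12}, the protocol article states: "Secondary outcome measures are the clinical pregnancy rate, miscarriage rate, and live birth rate". The live birth rate is the "number of normal fetuses delivered after 28 weeks of gestation" in relation "to the number of patients who received embryo transfer". The clinical pregnancy rate has the same denominator, but its numerator is pregnancies. The miscarriage rate is non-viable pregnancies ending before week 28 over clinical pregnancies.

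The word normal is not defined. The trial is open to patients and researchers; only the statisticians are blinded (Who will be blinded {17a}). The number of embryos per transfer is not fixed for this trial. The background says only: "Current clinical guidelines advise PGT-A and frozen single embryo transfers for women with age-related fertility concerns".

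On harms, Adverse event reporting and harms {22} says that all adverse events are recorded throughout, and adds: "Participants will be instructed to report any discomfort, unexpected symptoms, or complications during and after the intervention period". Table 1 marks adverse events at every time point up to 1 month postpartum. No outcome is defined for stillbirth, congenital anomaly or neonatal condition. The Discussion states that "the present study represents the first randomized controlled trial (RCT) to evaluate MVA supplementation in human-assisted reproduction".

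**The concern.** A live birth rate should say how many women, or how many transfers, led to a live-born child. This definition mixes that question with two others: whether the child is normal, and how many children were delivered. An undefined judgement of normality in an open-label trial also adds a subjective element to an outcome that should be objective.

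The Discussion concedes that the primary endpoint is a surrogate and says that pregnancy and live birth were added for that reason. If the live birth rate does not measure live birth, that safeguard is weakened. The intervention acts on the oocyte, so the child's condition is of direct interest. A definition that removes affected infants from the numerator, with no outcome that counts them, serves that interest poorly.

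**Working it through.** **1. The three definitions side by side (Outcomes {12}).**

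| Outcome | Numerator counts | Denominator counts |
|---|---|---|
| Clinical pregnancy rate | pregnancies | women with a transfer |
| Miscarriage rate | non-viable pregnancies before week 28 | clinical pregnancies |
| Live birth rate | normal fetuses delivered after week 28 | women with a transfer |

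Only the third counts fetuses over women. Its value for one woman can be 0, 1, 2 or more, so the ratio is not a proportion of women.

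**2. What each pregnancy result adds to the live birth numerator, read literally.**

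| Result for one woman | Per-woman live birth | Literal definition |
|---|---|---|
| Normal live-born singleton after week 28 | 1 | 1 |
| Normal live-born twins after week 28 | 1 | 2 |
| Live-born singleton with an anomaly after week 28 | 1 | 0 |
| Live birth before week 28 | 1 | 0, and not a miscarriage if the pregnancy was viable |
| Normally formed stillbirth after week 28 | 0 | not excluded by the wording |

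A stillbirth after week 28 is not a miscarriage either, so no outcome is defined for it.

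**3. Illustration with assumed counts.** The document gives no live birth figures. Assume N = 60 women transferred and W = 24 with at least one live-born infant, so the per-woman rate is 24/60 = 40.0%. Let T be twin deliveries, A live-born singletons with anomalies, E live births before week 28, and S normally formed stillbirths if counted. Then

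literal rate = (W + T + S − A − E)/N.

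- T = 2: 26/60 = 43.3%
- A = 2: 22/60 = 36.7%
- E = 1: 23/60 = 38.3%
- S = 1 and A = 1: 24/60 = 40.0%. The two cancel and the rate shows neither.

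These figures show direction and mechanism. They do not estimate what happens in this trial.

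**4. Can the document supply the size?** Its stated figures concern the primary outcome: "This study is designed to increase this euploid rate to 17% with a significance level (α) of 0.05", from about 10%. With two-sided α = 0.05 and power assumed at 80% (no power is stated), the unpooled two-proportion formula gives

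(1.960 + 0.842)² × (0.10 × 0.90 + 0.17 × 0.83)/0.07² = 370.2 before rounding up, so 371 per group.

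Then 371 × 1.1 = 408.1, and 2 × 408/5.45 = 149.7. The stated 371, 408 and 150 therefore reproduce, and none depends on the live birth definition.

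Transfers by dish can be guessed only with further assumptions: independent oocytes, the 17% target being true, 5.45/2 = 2.725 mature oocytes per dish, and a transfer from every dish with a euploid embryo.

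- Control: 150 × (1 − 0.90^2.725) ≈ 37 cycles
- MVA: 150 × (1 − 0.83^2.725) ≈ 60 cycles
- Either dish: 150 × (1 − 0.90^2.725 × 0.83^2.725) ≈ 82 cycles

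Since 37 + 60 = 97 exceeds 82, about 15 cycles are in both groups. On these denominators one event is worth 1/37 = 2.7 or 1/60 = 1.7 percentage points. That is the weight of any single event in a small group, not the bias from the definition.

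**The case against.** The strongest case on the other side has five parts.

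- **Infant harm.** A reader might infer that the plan hides it. The documents do not support this. The harms section records all adverse events and sends serious ones to the ethics committee within 24 hours, and Table 1 continues recording to 1 month postpartum. An anomaly could surface there. What stands is narrower: the harms text is worded around the participating women, and no defined outcome captures infant harm.
- **Stillbirths.** A reader might infer that they are counted. The outcome's own name argues against that. What stands is that the definition does not state the condition its name implies.
- **Test choice.** A reader might conclude that the plan applies a chi-square test to a ratio that is not a proportion. Statistical methods {20a} names clinical pregnancy, implantation and miscarriage as examples and does not mention live birth, so its test can only be inferred. The mismatch between fetuses and women does not depend on the test.
- **Condensed article.** Itemised neonatal fields may sit in forms or a full protocol not shown, so their absence is no finding. The live birth definition, however, is stated here in full and can be judged as it stands.
- **Frequency.** Twin births may be rare or absent. The document does not fix the number of embryos transferred, so this is unknown either way.

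**Conclusion.** The definition is wrong as written. From its wording alone, it excludes live-born infants judged not normal, counts a multiple birth more than once over a per-woman denominator, and leaves live births before week 28 in no outcome. It also fails to require explicitly that the infant is born alive.

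The size of the effect on the rate cannot be derived from the document. The shifts of a few percentage points shown above rest on assumed counts. Live birth is a secondary outcome without its own power calculation, so the primary outcome and sample size do not change. This is a correction that should be made, but it does not threaten the trial's main result.

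**What to change.** Reword the live birth outcome under Outcomes {12}:

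- Count a delivery with at least one live-born infant, regardless of the infant's condition, once per patient or once per transfer. State which unit is used, and use it in the denominator too.
- State a gestational cut-off that meets the miscarriage definition without a gap, so that every clinical pregnancy with a known end falls in exactly one category: miscarriage, stillbirth or live birth.
- Drop the word normal.
- Tabulate stillbirths, and any congenital anomalies recorded up to the 1-month postpartum contact, separately and by dish of origin of the transferred embryo. Report multiple births as their own count.

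The cost is mainly wording, since Table 1 already has secondary outcomes and adverse events at 1 month postpartum. One caveat applies: nothing in the article shows that anomaly status is asked about systematically there, so the table may have to rest on what was recorded, and should say so. Trial status places submission before the end of data analysis, with last follow-up in December 2025. If the analysis is still open, a dated clarification by the amendment route in section {25}, made before the statisticians learn the grouping, would suffice. If it is not, report both the published definition and the corrected one, and label them as such.

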### Participant timeline {13}

The participant timeline is shown in Table 1.

**Table 1 Tab1:** Participant timeline

Timepoint	Study period							
	T1	T2	T3	T4	T5	T6	T7	T8
	Oocyte retrival	in vitro fertilization	Embryo culture	Euploid blastocyst screening	Day of embryo transfer	14 days after transfer	28/42 days after transfer	1 month postpartum
Eligibility screen	×							
Informed consent	×							
Basic information login	×							
Randomization		×						
Embryo quality			×		×			
Primary outcome measure				×	×			
Serum HCG level						×		
Secondary outcome measure							×	×
Compliance assessment				×	×			
Adverse events	×	×	×	×	×	×	×	×

### Sample size {14}

Among women of AMA (38 ≤ age ≤ 42 years) undergoing treatment at this center, the current euploid blastocyst rate (defined as the number of euploid blastocysts per mature oocyte retrieved) is approximately 10%. This study is designed to increase this euploid rate to 17% with a significance level (α) of 0.05. To achieve this, each group is expected to include 371 mature oocytes, accounting for an estimated 10% dropout rate. This results in a final target of 408 mature oocytes per group. Given the average mature oocyte yield per cycle in women aged 38–42 years is approximately 5.45 oocytes, the study anticipates enrolling approximately 150 cycles in total.

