**Methods:**

The study will be conducted as a single-center, prospective, randomized controlled trial. A total of 128 infertile women aged 38–42 years undergoing PGT-A will be enrolled and randomized to either the MVA supplementation group or the control group. Cumulus-oocyte complexes retrieved from each cycle will be allocated according to the randomization protocol, with an estimated 150 cycles analyzed. The primary outcome is the euploidy blastocyst rate, while the secondary outcomes are the clinical pregnancy rate and live birth rate following frozen embryo transfer (FET).

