### Intervention description {11a}

A total of 150 PGT-A cycles will be included in the study. All retrieved COCs from each cycle will be randomly allocated into two parallel groups: the MVA supplementation group (intervention group) and the standard control group. Randomization will be performed at the level of sibling oocytes to minimize inter-individual variability.

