## Statistical methods

### Statistical methods for primary and secondary outcomes {20a}

Data analysis will be conducted using SPSS version 13.0. Descriptive statistics will summarize baseline demographic and clinical characteristics. Categorical variables—including clinical pregnancy rate, implantation rate, and miscarriage rate—will be compared between groups using the chi-square (*χ*^2^) test or Fisher’s exact test where appropriate. Continuous variables such as patient age, baseline FSH levels, antral follicle count (AFC), total gonadotropin dosage and duration, number of oocytes retrieved, and fertilization rate will be analyzed using independent-samples *t*-tests or nonparametric equivalents as appropriate. To account for potential confounding factors, multivariable regression analyses will be conducted. Logistic regression models will be applied for binary outcomes (e.g., clinical pregnancy, implantation, miscarriage), while linear regression will be used for continuous outcomes (e.g., number of mature oocytes, fertilization rate). Models will adjust for maternal age, baseline FSH levels, AFC, ovarian stimulation parameters, and other relevant covariates. For pregnancy outcomes, paternal factors such as age and semen parameters will also be included as covariates. A two-sided *p*-value < 0.05 will be considered statistically significant. Effect sizes will be reported with 95% confidence intervals. Sensitivity analyses will be conducted to test the robustness of the results.

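### The 10% dropout allowance multiplies 371 by 1.1 instead of dividing by 0.9, so the target of 408 mature oocytes per group leaves 367, slightly below the stated requirement

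*Protocol article*

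**What the plan says.** Sample size {14} starts from a euploid blastocyst rate of about 10% per mature oocyte at the centre and sets the target: "This study is designed to increase this euploid rate to 17% with a significance level (α) of 0.05". The test is two-sided, which appears only in the statistical methods section {20a}: "A two-sided *p*-value < 0.05 will be considered statistically significant".

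On numbers, {14} says that "each group is expected to include 371 mature oocytes, accounting for an estimated 10% dropout rate", and then: "This results in a final target of 408 mature oocytes per group". It converts this to cycles with a mean yield of 5.45 mature oocytes per cycle, arriving at roughly 150 cycles. The intervention description {11a} repeats the cycle count: "A total of 150 PGT-A cycles will be included in the study". The abstract gives 128 women together with an estimated 150 cycles. The article states no power.

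**The concern.** A dropout allowance should ensure that the number left after the expected loss is the number the power calculation asked for. Multiplying by one plus the dropout rate does not do that, because the loss is then taken from the larger, inflated number. The target in {14} therefore misses its own requirement at the dropout rate that it assumes.

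The wording makes this hard to see. The sentence that introduces 371 can be read as saying that dropout is already included, while the next sentence raises the number to 408. With no power given, a reader must reconstruct the calculation to learn which figure is the evaluable number and what it delivers. At stake is a correct statement of the trial's planned size and power, which readers will need when they interpret the primary result, above all a null one.

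**Working it through.** **Inputs**
- From {14}: control rate p1 = 0.10; target rate p2 = 0.17; α = 0.05; 371 per group; 10% dropout; 408 per group; 5.45 mature oocytes per cycle; about 150 cycles.
- From {20a}: two-sided test.
- From Trial design {8}: 1:1 allocation of oocyte complexes within subject.
- Assumed: 80% power, found by back-calculation.

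**Step 1. Reproduce 371.** Two independent proportions, unpooled variance:

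n = (z₀.₉₇₅ + z₀.₈₀)² × [p1(1−p1) + p2(1−p2)] / (p2−p1)²

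= (1.960 + 0.842)² × (0.0900 + 0.1411) / 0.07²

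= 7.849 × 0.2311 / 0.0049 = 370.2, rounded up to **371**. This matches the stated figure.

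Alternatives, two-sided unless noted:

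| Method | Power | n per group |
|---|---|---|
| Unpooled | 80% | 371 |
| Pooled | 80% | 373 |
| Arcsine | 80% | 369 |
| Continuity-corrected | 80% | 401 |
| Unpooled | 85% | 424 |
| Unpooled | 90% | 496 |
| One-sided, continuity-corrected | 85% | 370 |

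The last row comes close, but a one-sided test conflicts with {20a}. The unpooled two-sided formula at 80% is the only exact match, so 371 is the evaluable number before any dropout.

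**Step 2. Reproduce 408 and 150.**
- 371 × 1.10 = 408.1, stated as 408.
- 2 × 408 = 816; 816 / 5.45 = 149.7, stated as about 150 cycles.

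Both match. Dropout was applied once, as n × (1 + d).

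**Step 3. Apply the stated loss to the stated target.**
- 408 × 0.90 = 367.2, or **367** evaluable per group.
- Shortfall: 371 − 367 = 4 per group.

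**Step 4. Correct inflation.**
- n / (1 − d) = 371 / 0.90 = 412.2, rounded up to **413** per group. Check: 413 × 0.90 = 371.7.
- Total: 2 × 413 = 826 oocytes; 826 / 5.45 = 151.6, or about **152 cycles**.
- Difference from the stated plan: 413 − 408 = 5 oocytes per group (1.2%) and 152 − 150 = 2 cycles.

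**Step 5. Effect on power.** Unpooled power = Φ(0.07 / √(0.2311/n) − 1.960):
- n = 371: 0.07 / 0.02496 = 2.805; Φ(0.845) = **80.1%**.
- n = 367: 0.07 / 0.02509 = 2.790; Φ(0.830) = **79.7%**.

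The loss is about 0.4 percentage points. The pooled formula gives the same difference (79.8% against 79.4%).

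**Step 6. Women and cycles.**
- 150 × 5.45 = 817.5, which covers the 816 oocytes in the plan.
- 150 − 128 = 22 cycles beyond one per woman, or 150/128 = 1.17 cycles per woman. The article does not say where these cycles come from.

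**The case against.** The strongest objection is that the discrepancy is smaller than the precision of its inputs. The 10% rate, the 5.45 yield and the 150 cycles are all described as approximate, and the dropout rate as an estimate. A mean yield of 5.51 (826/150) instead of 5.45 would close the whole gap without another cycle. That is true, and it is why the point is minor. It does not make the inflation step correct: 408 less 10% is 367 whatever the precision of the other inputs.

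A reader might infer more than this, in four ways that the document does not support.

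- *That the sample-size figures as a whole fail.* They do not: 371, 408 and 150 each reproduce, the first with 80% power assumed.
- *That dropout is counted twice.* The back-calculation shows 371 as the number before dropout and 408 as the number after it. The text describes a single adjustment in loose words.
- *That 128 women cannot supply the oocytes.* That needs one cycle per woman (128 × 5.45 = 698), and the article states no such limit. Table 1 shows a single retrieval, but it is a visit schedule and sets no limit on cycles. The abstract gives 128 women and an estimated 150 cycles together, and {14} and {11a} size the trial in cycles. The eligibility limit of two IVF/ICSI cycles {10} does not settle whether a woman may contribute two study cycles, so the link between the two counts is unexplained but not contradictory.
- *That treating oocytes as independent makes the trial underpowered.* Allocation within a woman can gain precision through pairing, while correlation among oocytes can lose it. The article gives no correlation from which to judge the balance, so even the direction is unknown. This is an assumption to disclose, and no error has been shown.

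A further objection is that a condensed article may leave the power and the cycle accounting to the full protocol. That is fair, and neither omission is the finding here. They belong in the restatement because the corrected sentence is unclear without them.

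**Conclusion.** The point holds in a narrow form. The dropout inflation in {14} is wrong: the stated target leaves 367 evaluable mature oocytes per group, not 371, and a correct allowance gives 413 per group, 826 in total and about 152 cycles. The cost is 4 evaluable oocytes per group and about 0.4 points of power, from 80.1% to 79.7%. This does not threaten the trial's ability to test its primary hypothesis.

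These figures rest on 80% power (inferred), a two-sided 5% test of 10% against 17%, an unpooled normal approximation, and independent oocytes. The inflation error itself depends on none of these assumptions, since it follows from 371, 408 and 10% alone.

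**What to change.** Restate the figures in Sample size {14}:

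1. Say that 371 per group is the evaluable number before dropout. Give the power and method, apparently 80%, two-sided 5%, two proportions with unpooled variance; the authors should confirm this.
2. Choose one of two statements on dropout. Either a 10% loss requires 413 per group (826 oocytes, about 152 cycles), or the planned 408 per group (about 150 cycles) leaves about 367 after a 10% loss, with just under 80% power. The second fits better, because Trial status reports that recruitment ended in May 2024 and the last biopsy was done in January 2025. It keeps the prospective target visible and corrects only what is claimed for it.
3. Add one clause saying that the calculation treats sibling oocytes as independent.
4. Give women and cycles together in the abstract, {11a} and {14}: 128 women and an estimated 150 cycles, with about 22 women contributing a second cycle if that is what happened. Keep 150 as an estimate unless the achieved number is known, since the article does not report that 150 cycles were obtained.

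The cost is a few sentences and a slightly less favourable power statement. No extra patients, cycles or data are needed.
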